## 6.2 Operative assessments and data collection

The part of operative information in the CRFs will be completed. This collects data relating to the operation including:

1. Surgeon;
2. ASA status;
3. Thoracoscopic technique (robotic-assisted or video-assisted);
4. Whether there is an intraoperative change of surgical plan (inappropriateness for minimally invasive lobectomy based on intraoperative exploration, such as sublobar resection for a small lesion or extensive lung resection for a massive tumor);
5. Duration of operation;
6. Whether outcome of operation curative, palliative or unresectable;
7. Whether conversion to open surgery occurred, and reason;
8. Any intraoperative complications.

## 6.3 Pathology assessment

The pathology assessment is accorded with the 2015 World Health Organization (WHO) Classification of Tumors of the Lung, Pleura, Thymus, and Heart^13^. The part of pathology information in the CRFs will be completed. This collects data relating to the pathology including:

1. Gross description including sample size and tumor size;
2. Histology including type and differentiation;
3. Metastatic spread including lymph nodes (number retrieved and number involved), lymphatic or vascular invasion, neural invasion, pleural invasion;
4. Co-existent conditions (e.g., granuloma necrosis);
5. Pathological TNM stage (the eighth edition of the TNM classification for lung cancer^12^, Appendix 1).

## 6.4 Postoperative assessment and data collection

Postoperative care has been described before (see section 5.3). A postoperative clinical assessment must be carried out for all patients and the data collected will include:

1. Duration of postoperative hospital stay (date fit for discharge, actual discharge date, reason for any delay);
2. Postoperative complications and severity;
3. Details of any further surgery or invasive operation required and reason.

## 6.5 Follow-up assessment and data collection

Follow-up data will be collected every 6 months after surgery until patient death or the completion of the study.

Data collected will include:

1. Patient status (alive or dead) and details of death, including:

- Date of death
- Reason of death (NSCLC related or other)

1. Details of any adjuvant therapy;
2. Details of any local or distant recurrence, including:

- Date of recurrence
- Site of recurrence
- Method of diagnosis
- Treatment for recurrence

## 6.6 Assessment of health-related quality of life and postoperative pain

Patients will be asked to complete the generic HRQoL and pain questionnaires.

For the assessment of HRQoL, three HRQoL instruments are used: the European Organization for Research and Treatment of Cancer Quality of Life Questionnaire (EORTC QLQ-C30) version 3.0^14^, the EORTC Quality of Life Questionnaire in Lung Cancer (EORTC QLQ-LC13),^15^ and the European Quality of Life 5 Dimensions (EQ-5D) questionnaire.^16^ This will be done before surgery and at weeks 4, 24, and 48 postoperatively.

For pain evaluation, an 11-point visual analog score (VAS) (on postoperative day 1) and numeric rating scale (NRS) (used during follow-up) are used, with a score of 0 representing “no pain” and a score of 10 signifying the “worst pain imaginable”. The pain assessment is done at week 4, 24, and 48 postoperatively.

## 6.7 Complications and safety reporting

For the purpose of this trial, the safety reporting terms adverse events and serious adverse events have been translated into complications.

**6.7.1 General definitions**

A complication is defined as an untoward medical event in a patient, which has a causal relationship to the trial. The trial includes the surgical intervention and procedures directly related to the surgery (e.g., anesthetic) and any trial specific interventions (e.g., the consent process and completion of questionnaires).

The grade of complications is evaluated using the Clavien-Dindo classification (Appendix 4),^17^ and will be assessed by counting the number of patients presenting with one or more complications. The total numbers of complications and each grade will be specified.

A serious complication is defined as a complication which:

1. results in death within 90 days of surgery irrespective of its association with surgery
2. is life-threatening
3. requires unplanned in-patient hospitalization or prolongation of existing hospitalization due to early postoperative complications
4. requires reoperation due to early postoperative complications
5. results in persistent or significant disability or incapacity
6. is otherwise considered medically significant by the investigator

**6.7.2 Expected complications**

**Operative**

- Damage to organ/structure e.g.
- Heart
- Pericardium
- Diaphragm
- Major vessels
- Nerves
- Hemorrhage
- Failure of surgical equipment (robotic system or thoracoscopic equipment, including hardware/software malfunction)

**Postoperative**

- Subcutaneous emphysema
- Pulmonary air leak
- Pneumonia
- Hemorrhage
- Wound infection
- Pleural effusion
- Pneumothorax
- Hypoxemia
- Acute renal failure
- Cerebrovascular attack/stroke
- Disseminated intravascular coagulation
- Sepsis
- Delerium
- Urinary retention

**Other**

- Acute renal failure
- Cardiac arrhythmia
- Cardiac failure
- Ischemic heart disease/myocardial infarction
- Pulmonary embolus
- Respiratory failure
- Urinary tract infection

**6.7.3 Reporting of complications**

Information on all complications will be collected for this trial whether volunteered by the patient, discovered by investigator questioning or detected through physical examination, laboratory test or other investigation.

**6.7.4 Responsibilities for safety reporting**

Complications should be reported based on relevant regulations. The physician in charge should hold accountability and responsibility for the emergency treatment of patients with any degree of complications to ensure patient safety.

**Reporting of serious complications**

Serious complication is defined in section 6.7.1. Serious complication should be recorded and reported in following procedures:

1. The physician in charge or the study monitor who has confirmed any serious complication encountered must report it immediately to the principal investigator ([name]). If the principal investigator cannot be contacted, the physician in charge or the study monitor must act on his behalf.
2. The principal investigator or his designee must complete the “Serious Complication Report” form and submit it to the IRB for further assessment within 24 hours of becoming aware of the serious complication (Appendix 5).
3. The IRB, along with the principal investigator and other members of the study team, on determining the urgency, importance, causality, and degree of impact of the report, will discuss the necessity of suspending further enrollment or even termination of the study. The discussion will be held within 24 hours of the submission of the “Serious Complication Report” form.

**Reporting of nonserious complications**

For nonserious complications, regular reporting obligations should be followed:

1. The physician in charge or the study monitor who has confirmed any nonserious complication should record the type and degree of the complication in the CRF.
2. The principal investigator, along with other members of the surgery team, will have a review and discussion about the presenting nonserious complications on a weekly basis, to confirm whether there is an under-reporting and misjudgment of the nonserious complications.

# 7. STATISTICAL CONSIDERATIONS

## 7.1 Statistical hypotheses

This one-arm trial aims to test the safety and feasibility of conversion surgery after induction therapy for locally advanced and advanced non-small cell lung cancer. Our hypothesis is that more than 90% patients will reach R0 resection with acceptable surgical-related morbidity, MPR/pCR rate, and 1-year DFS/OS. There may be difference towards DFS/OS between the MPR and non-MPR cohort.

## 7.2 Sample size estimation

Regarding the exploratory nature of this study, a sample size of 30 patients was determined.

## 7.3 Statistical analysis principles

All statistical analyses will be performed using SPSS 22.0 (IBM), R (version3.5.3, R Foundation for Statistical Computing, Vienna, Austria) or GraphPad Prism version 8.0.0 for Windows (GraphPad Software). The significance level for testing differences between the two groups will be set at α=0.05 (bilateral). A significance level of P < 0.05 will be considered statistically significant, and a 95% confidence interval (CI) will be used.

Categorical variables will be summarized by descriptive statistics, including the number of participants, number of events, and percentage. We will use Pearson Chi-squared test or Fisher exact test to compare the difference between the two groups.

Continuous variables following a normal distribution will be presented as mean ± standard deviation (SD), and the Student’s t-test was used for comparison. In cases of noncompliance with the normal distribution, continuous variables will be presented as medians (interquartile range [IQR]) and compared using the Wilcoxon rank-sum test between the two groups.

Regarding the survival data, the Kaplan-Meier approach will be used to calculate OS and DFS at 1, 2, 3, 4, and 5 years. The estimates of median survival time will be provided. Survival curves will be compared using the log-rank test. The Cox proportional hazard regression model will be used to calculate the hazard ratio (HR) and the corresponding 95% CI.

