***Statistical Analysis***

Continuous variables which is normally distributed will be presented as mean ± standard deviation, and Student’s t-test will be used for comparison in subgroup analysis. In cases of non-compliance, continuous variables will be presented as median (interquartile range), and compared by Wilcoxon rank-sum test between subgroups. Categorical variables were presented as frequency with percentage. The test level between the subgroups will be set at α=0.05 (bilateral), and differences with P <0.05 will be considered to be statistically significant.

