**2.2.1 Rationale for study population**

This study is a single-arm clinical trial. The aim of this study is to evaluate the safety and feasibility of salvage surgery after induction therapy for locally advanced and advanced non-small cell lung cancer. Due to the lack of previous studies for reference, the sample size is not calculated based on hypothesis testing. Regarding the exploratory nature of this study, a sample size of 30 patients was determined.

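### Sections 7.3 and 1.1 use the equal-variance Student's t-test with no provision for unequal variances, so its level is off if subgroup sizes and SDs both differ

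*Combined protocol and SAP*

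**What the plan says.** Section 7.3 sets a rule that depends on the distribution. A variable judged normal is summarised by its mean and SD, and the text goes on: "Student’s t-test was used for comparison. In cases of noncompliance with the normal distribution, continuous variables will be presented as medians". Those medians come with the IQR, and the variable is then "compared using the Wilcoxon rank-sum test between the two groups". The level is given in the same section: "The significance level for testing differences between the two groups will be set at α=0.05 (bilateral"). The statistical paragraph of the synopsis (section 1.1) has the same rule and places it in the subgroup setting: "Student’s t-test will be used for comparison in subgroup analysis".

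Neither place names a normality test or its cut-off, a check on variances, or an unequal-variance form of the t-test.

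The study has one arm, so the two groups in section 7.3 must be subgroups of the enrolled patients. Their definition and sizes are not given for any continuous outcome. The one contrast that is named, in section 7.1, concerns survival: "There may be difference towards DFS/OS between the MPR and non-MPR cohort". On size, section 7.2 says "Regarding the exploratory nature of this study, a sample size of 30 patients was determined", and section 2.2.1 adds that "the sample size is not calculated based on hypothesis testing".

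**The concern.** Student's t-test pools the two sample variances and so assumes that the groups have the same spread. Judging normality does not test that assumption: two normal samples with very different SDs both pass.

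The pooled variance is dominated by the larger group. If the smaller group is the more variable one, the standard error is too small and there are too many false positives. If the larger group is the more variable one, the standard error is too large and the test becomes too strict. The 95% confidence interval for the mean difference goes wrong in the same way.

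Subgroups formed from patient or outcome characteristics have no allocation ratio to keep them balanced. The continuous outcomes that could be compared include operation time, blood loss, postoperative stay, lymph node counts, and the questionnaire and pain scores of section 6.6. At stake are the P values and intervals for those comparisons. Section 7.3 would call any of them significant at P < 0.05.

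**Working it through.** **Inputs from the documents.** N = 30 (section 7.2); two-sided α = 0.05 and Student's t-test for variables judged normal (section 7.3). The plan has no figure to reproduce here: N is not derived from a test, and no power, effect size or SD is stated.

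**Inputs assumed.** Subgroup splits, SD ratios and, for the full two-step rule, Shapiro-Wilk at 0.05. None is in the documents, so a range is shown.

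**Step 1: why the level moves.** With group sizes n1, n2 and true SDs s1, s2:

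- variance of the mean difference that Student's test estimates, on average: [(n1 − 1)s1² + (n2 − 1)s2²]/(n1 + n2 − 2) × (1/n1 + 1/n2)
- true variance of the mean difference: s1²/n1 + s2²/n2

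If s1 = s2, the two expressions are identical for any split. If n1 = n2, they are also identical for any SDs. They part only when sizes and SDs both differ.

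Take 22 v 8, with 1/22 + 1/8 = 0.1705:

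- *Smaller group has twice the SD.* Pooled variance (21×1 + 7×4)/28 = 1.75; estimated 1.75 × 0.1705 = 0.298; true 1/22 + 4/8 = 0.545. The true standard error is √(0.545/0.298) = 1.35 times the estimated one. The critical value 2.048 (28 df) then acts like 2.048/1.35 = 1.51, a normal two-sided tail of about 13%.
- *Larger group has twice the SD.* Pooled variance (21×4 + 7×1)/28 = 3.25; estimated 3.25 × 0.1705 = 0.554; true 4/22 + 1/8 = 0.307. The ratio is √(0.307/0.554) = 0.744, and 2.048/0.744 = 2.75, a tail of about 0.6%.

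This approximation ignores the sampling error of the pooled variance, so simulation supplies the figures to use.

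**Step 2: simulated false-positive rates.** Normal data, equal means, 200,000 replicates per cell. Each Student cell gives the rate when the smaller group has the smaller SD / the larger SD.

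| Split | SD ratio | Student | Welch |
| --- | --- | --- | --- |
| 15/15 | 1.5 to 3 | 5.1% to 5.6% | 4.9% to 5.1% |
| 18/12 | 2 | 3.0% / 8.5% | 5.0% / 5.0% |
| 20/10 | 1.5 | 2.7% / 8.5% | 4.9% / 5.1% |
| 20/10 | 2 | 1.9% / 11.4% | 5.0% / 5.1% |
| 22/8 | 1.5 | 2.0% / 10.2% | 4.9% / 5.2% |
| 22/8 | 2 | 1.1% / 14.7% | 4.9% / 5.2% |
| 25/5 | 2 | 0.4% / 20.7% | 5.2% / 5.6% |
| 15/15 to 25/5 | 1 (equal SDs) | 4.9% to 5.1% | 4.9% to 5.7% |

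For the interval, coverage is 100% minus the rejection rate. A nominal 95% interval from Student's test at 22/8, ratio 2, covers in 100 − 14.7 = 85.3% or 100 − 1.1 = 98.9% of trials.

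**Step 3: is the normality step to blame?** Full two-step rule, 10,000 replicates per cell:

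- equal SDs, normal data: 4.8% to 5.2%
- identical skewed (lognormal) data in both groups: 4.1% to 5.3%
- 22/8, SD ratio 2: 1.1% / 14.8% with normality judged per group, 1.2% / 11.4% with it judged on the pooled data

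So the distortion comes from the pooled variance. The normality step does not repair it, and adds little of its own.

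**Step 4: does the rank test escape?** No. At 20/10 and 22/8 with SD ratios 1.5 and 2, Wilcoxon rejects in about 2% to 9%: less distorted than Student's test, but not at 5%.

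**Step 5: price of Welch when variances are equal.** True difference 1 SD: power falls from 70.4% to 68.5% at 20/10 (1.9 points) and from 64.7% to 60.8% at 22/8 (3.9 points).

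**The case against.** The best defence has four parts.

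1. *The driving inputs are not in the plan.* Subgroup sizes, SDs and SD ratios are all assumed. This stands. At 18/12 with ratio 2 the range is only 3.0% to 8.5%, and at 15/15 there is almost no error. A reader might infer that 30 patients in unequal groups by themselves produce false-positive rates of 1% to 15%. The documents do not support that: with equal SDs, Student's test keeps its level at every split examined.

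2. *Choosing between t-test and rank test by distribution is common practice.* This stands as far as the level is concerned. A reader might blame the normality check for the inflation, but step 3 shows that the two-step rule holds about 5% when the groups share a distribution, skewed or not. What remains is that the check is unnamed, so the choice between mean and median is left until the data are seen. That is a matter of clarity.

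3. *Little depends on these tests.* This stands and sets the severity. The primary endpoint is a percentage, and the only named contrast, MPR v non-MPR, is for DFS and OS, which section 7.3 analyses by log-rank and Cox methods. A reader might carry the concern over to the trial's main conclusions; nothing in the documents links them to a t-test.

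4. *Moving skewed variables to Wilcoxon in advance would not cure the problem.* This also stands (step 4), so that step is not put forward as the remedy.

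The label of exploratory study does not dispose of the point: section 7.3 still attaches a 0.05 level and a 95% confidence interval to these comparisons, and a test that keeps its level is available at little cost.

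**Conclusion.** The point holds conditionally and is minor. The plan specifies the equal-variance t-test with no alternative, for subgroups whose sizes nothing balances. If sizes and SDs both differ, the level is wrong in a direction set by which group is more variable: about 1% or 15% at 22 v 8 and about 2% or 11% at 20 v 10, both with SD ratio 2. Welch's test stays at 4.9% to 5.7% in every setting simulated.

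These figures rest on assumed splits and SD ratios and on normal data. They are not bounds: 18 v 12 gives less distortion and 25 v 5 gives more. The effect is confined to exploratory subgroup comparisons of secondary continuous outcomes.

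**What to change.** In section 7.3 and in the statistical paragraph of section 1.1, replace Student's t-test by Welch's t-test, and state that the mean difference will be reported with its Welch 95% confidence interval. This is a wording change. The only statistical cost is the power loss in step 5, about 2 points at 20/10 and 4 at 22/8, and it arises only if variances are equal.

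Optionally, fix the summary and test for each variable in advance (mean with Welch, or median with Wilcoxon) instead of letting an unnamed normality check decide. That makes the reporting predictable. It would not by itself remove the effect of unequal spread, since Wilcoxon is affected as well.

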## 7.4 Missing data strategy

Missing data will not be imputed.

## 7.5 Statistical analysis set

An intention-to-treat analysis will be performed. All included participants who meet the eligibility will be included in the final analysis. Patients who do not comply with the protocol will be analyzed in their initial treatment arm. These patients will have to be regularly followed up according to the protocol.

## 7.6 Interim analysis

No scheduled interim analysis will be conducted in this study.

# 8. ETHICAL CONSIDERATIONS

This study will be carried out upon approval of the IRB and in compliance with the Helsinki Declaration, applicable GCP guidelines, and applicable laws and regulations. Patients can participate in the study only after having signed the informed consent form in full awareness of the objectives of the study and the risks involved. Informed written consent will be obtained from the patients prior to randomization into the trial. The right of a patient to refuse participation without giving reasons must be respected. The patient must remain free to withdraw at any time from the trial without giving reasons and without prejudicing his/her further treatment. All information collected during the course of the trial will be kept strictly confidential.

## 8.1 Responsibilities of investigators

The investigators are responsible for the conduction of this study. The investigators will ensure the implementation of this study in accordance with the study protocol and in compliance with the Declaration of Helsinki, as well as domestic ethical guiding principles and applicable regulatory requirements. It is specially noted that, the investigators must ensure that only subjects who provide informed consent and fulfill the eligibility criteria can be enrolled in this study.

## 8.2 Compensation

Health injury incurred by participating in the present clinical trial will be treated appropriately according to the symptoms in the way as normal medical care and will be covered by the national health insurance scheme. Any medical expenses not covered by the national health insurance scheme will be incurred by the patient. As this is a clinician-led trial there are no arrangements for no-fault compensation.

# 10. APPENDICES

Appendix 1 The eighth edition of the TNM classification for lung cancer

Appendix 2 The American Society of Anesthesiologists (ASA) Physical Status Classification

Appendix 3 English model of informed consent form

Appendix 4 The Clavien-Dindo classification of surgical complication

Appendix 5 English model of serious complication report form

## Appendix 1 The eighth edition of the TNM classification for lung cancer

(From Goldstraw P, et al. J Thorac Oncol. 2016 Jan;11(1):39-51.)

| **T: Primary tumor** |  |
| --- | --- |
| Tx | Primary tumor cannot be assessed or tumor proven by presence of malignant cells in sputum or bronchial washings but not visualized by imaging or bronchoscopy |
| T0 | No evidence of primary tumor |
| Tis | Carcinoma in situ |
| T1 | Tumor ≤3 cm in greatest dimension surrounded by lung or visceral pleura without bronchoscopic evidence of invasion more proximal than the lobar bronchus (i.e., not in the main bronchus) |
| T1a (mi) | Minimally invasive adenocarcinoma |
| T1a | Tumor ≤1 cm in greatest dimension |
| T1b | Tumor >1 cm but ≤2 cm in greatest dimension |
| T1c | Tumor >2 cm but ≤3 cm in greatest dimension |
| T2 | Tumor >3 cm but ≤5 cm or tumor with any of the following features:  - Involves main bronchus regardless of distance from the carina but without involvement of the carina  - Invades visceral pleura  - Associated with atelectasis or obstructive pneumonitis that extends to the hilar region, involving part or all of the lung |
| T2a | Tumor >3 cm but ≤4 cm in greatest dimension |
| T2b | Tumor >4 cm but ≤5 cm in greatest dimension |
| T3 | Tumor >5 cm but ≤7 cm in greatest dimension or associated with separate tumor nodule(s) in the same lobe as the primary tumor or directly invades any of the following structures:  chest wall (including the parietal pleura and superior sulcus tumors), phrenic nerve, parietal pericardium |
| T4 | Tumor >7 cm in greatest dimension or associated with separate tumor nodule(s) in a different ipsilateral lobe than that of the primary tumor or invades any of the following structures:  diaphragm, mediastinum, heart, great vessels, trachea, recurrent laryngeal nerve, esophagus, vertebral body, and carina |
| **N: Regional lymph node involvement** |  |
| Nx | Regional lymph nodes cannot be assessed |
| N0 | No regional lymph node metastasis |
| N1 | Metastasis in ipsilateral peribronchial and/or ipsilateral hilar lymph nodes and intrapulmonary nodes, including involvement by direct extension |
| N2 | Metastasis in ipsilateral mediastinal and/or subcarinal lymph node(s) |
| N3 | Metastasis in contralateral mediastinal, contralateral hilar, ipsilateral or contralateral scalene, or supraclavicular lymph node(s) |
| **M: Distant metastasis** |  |
| M0 | No distant metastasis |
| M1 | Distant metastasis present |
| M1a | Separate tumor nodule(s) in a contralateral lobe; tumor with pleural or pericardial nodule(s) or malignant pleural or pericardial effusion |
| M1b | Single extrathoracic metastasis |
| M1c | Multiple extrathoracic metastases in one or more organs |

| **T/M** | Subgroup | **N0** | **N1** | **N2** | **N3** |
| --- | --- | --- | --- | --- | --- |
| **T1** | **T1a**≤1cm | IA1 | IIB | IIIA | IIIB |
|  | 1cm<**T1b**≤2cm | IA2 | IIB | IIIA | IIIB |
|  | 2cm<**T1c**≤3cm | IA3 | IIB | IIIA | IIIB |
| **T2** | 3cm<**T2a**≤4cm | IB | IIB | IIIA | IIIB |
|  | 4cm<**T2b**≤5cm | IIA | IIB | IIIA | IIIB |
| **T3** | 5cm<**T3**≤7cm | IIB | IIIA | IIIB | IIIC |
| **T4** | 7cm<**T4** | IIIA | IIIA | IIIB | IIIC |
| **M1** | **M1a** | IVA | IVA | IVA | IVA |
|  | **M1b** | IVA | IVA | IVA | IVA |
|  | **M1c** | IVB | IVB | IVB | IVB |

